# Motivating smokers at outdoor public smoking hotspots to have a quit attempt with a nicotine replacement therapy sample: study protocol for a randomized controlled trial

**DOI:** 10.1186/s13063-016-1485-z

**Published:** 2016-07-26

**Keywords:** Intervention, Nicotine replacement sample, Smoking cessation, Smoking hotspots

## Abstract

**Background:**

About half of the daily smokers in Hong Kong have never tried and have no intention to quit smoking. More than one-third (37.9 %) of daily smokers have attempted to quit but failed. Nicotine replacement therapy (NRT) is a safe and effective pharmacotherapy to increase abstinence by reducing withdrawal symptoms during the early stage of smoking abstinence. However, the prevalence of NRT use in Hong Kong is lower than in most developed countries. The proposed study aims to assess the effectiveness of providing free NRT samples to smokers on increasing quit attempts and the quit rate.

**Methods:**

Trained university undergraduate students as ambassadors will invite smokers at outdoor public smoking hotspots to participate in the randomized controlled trial, in which eligible smokers will be randomized to receive a 1-week free NRT sample and medication counselling (intervention) or advice to purchase NRT on their own (control). The primary outcome is self-reported quit attempts (no smoking for at least 24 hours) in the past 30 days at 1-month and 3-month telephone follow-up.

**Discussion:**

The findings will inform the effectiveness of delivering free NRT samples at outdoor public smoking hotspots to increase quit attempts and abstinence. The study will also provide information on smokers’ adherence to the NRT sample, side effects and safety issues related to the usage. This will improve the design of a large trial to test the effect of the NRT sample.

**Trial registration:**

ClinicalTrials.gov NCT02491086. Registered on 7 July 2015.

**Electronic supplementary material:**

The online version of this article (doi:10.1186/s13063-016-1485-z) contains supplementary material, which is available to authorized users.

## Background

Each year over 5000 deaths are attributable to active smoking in Hong Kong [1]. Quitting smoking is the most effective preventive medicine to reduce the burden of many non-communicable diseases. Hong Kong has the lowest smoking prevalence (10.7 % daily smokers) in the developed world due to the strong tobacco measures enacted in the past few decades [2], but over half (53 %) of daily smokers in Hong Kong have never tried and have no intention to quit smoking [3]. More than one-third (37.9 %) of daily smokers have attempted to quit but failed [3].

Enforcement of the indoor smoking ban led to increased smoking behaviour in outdoor public areas, namely smoking hotspots, where an ashtray is available [4, 5]. These outdoor hotspots were observed in Hong Kong due to the high population density and relatively warm weather throughout the year. Nevertheless, the increased outdoor smoking allows easier identification of smokers and makes way for a face-to-face approach to proactively offer cessation advice outdoors. Since 2009, our research team and the Hong Kong Council on Smoking and Health have organized the ‘Quit to Win’ Contest to promote smoking cessation each year and deliver brief smoking cessation advice for the smokers at these hotspots. This approach recruited 1003 smokers in 3 months to participate in a randomized trial testing the effectiveness of a cash incentive and a brief smoking cessation intervention, and yielded a quit rate of 20 % at 6-month follow-up [6] which warrants development of simple interventions in this setting.

Nicotine is highly addictive and many smokers are unable to quit successfully due to withdrawal symptoms. Nicotine replacement therapy (NRT) is a safe and effective pharmacotherapy to reduce these symptoms during early abstinence and to increase the quit rate in the longer term [7–9]. In Hong Kong, NRT is included in the Hospital Authority Drug Formulary, and can be purchased legally over the counter in a pharmacy or prescribed freely from the Tobacco Control Office’s Quitline and many other smoking cessation clinics. However, the prevalence of using NRT in Hong Kong is lower than in most developed countries. In smokers who had previous quit attempts, 96.8 % tried to quit with ‘self-determination’ and only 23.1 % used prescribed or over-the-counter medication [3]. On the contrary, the corresponding percentage of quitting with medication is at least 40 % in Australia, Canada, the UK, and the USA [10]. The low prevalence of using NRT in Hong Kong may be due to the higher price of NRT per day ($5.43 per day) [11] than, say, in the USA (US$2.41–3.62 per day) [12]. Very few smokers therefore use NRT for their quit attempts, especially those who do not prefer to obtain free NRT from the smoking cessation clinics.

The standard duration of using NRT for smoking cessation is 12 weeks [13, 14]. Providing free NRT for 1 or 2 weeks (i.e. a NRT sample) to motivate smokers to quit is theoretically based on catastrophic theory, suggesting that quitters do not necessarily go through the stages of quitting readiness according to the transtheoretical model [15], but their quit attempts can be initiated by various environmental cues such as sickness [16] and pregnancy [17]. Brief smoking cessation advice and free medication might stimulate smokers to start quitting. Two recent US randomized controlled trials (RCTs) found that a NRT sample increased quitting motivation, confidence and quit attempts in smokers who were not motivated to quit, compared with those who did not receive the sample [18, 19].

The NRT sample might also be beneficial for smokers who have just developed the motivation to quit and will act soon. The Clinical Practice Guideline for smoking cessation recommends that clinicians should advise all smokers to use effective medication for tobacco dependence treatment [13]. Smokers who started to quit shortly after they decided to quit had a higher likelihood of achieving long-term abstinence than smokers who had longer latency between their quitting decision and action [20–22]. Providing a NRT sample and information on NRT for these motivated smokers might be a timely intervention to help them reduce any physical discomfort during quitting and hence increase their abstinence.

Misconception about the safety and efficacy of NRT is associated with a lower interest in using the medication for quit attempts [23–25]. Nearly half of the smokers thought that NRT was as dangerous as cigarettes, and hence underestimated its efficacy to increase quitting success [21]. Providing sufficient and scientific information on NRT is therefore important to enhance the adherence to the NRT. We also suggest that increasing literacy in medication, and enhancing smokers’ experience in using cessation aids are beneficial. Because both abrupt and gradual cessation with NRT are effective to increase abstinence for motivated and unmotivated smokers [26, 27], NRT users should be well informed about these approaches while making their own decisions.

We propose to conduct a RCT to evaluate the effectiveness of a NRT sample in adult smokers recruited at smoking hotspots. The setting for the recruitment and intervention of the proposed RCT will be similar to the aforementioned Quit to Win Contest, but we will use a free NRT sample as the major intervention instead of a cash incentive. The primary research questions of the present RCT are: will a NRT sample increase quit attempts and abstinence in smokers who are smoking at smoking hotspots; and will a NRT sample increase motivation to quit?

## Methods

### Trial design

The study aims to motivate smokers to have a quit attempt with a free NRT sample. We will firstly train nurses and university undergraduate students as outreach smoking cessation ambassadors, who will proactively approach the smokers at outdoor smoking hotspots of urban areas, where rubbish bins with a collector of cigarette butts are nearby, and invite them to participate in the two-arm, parallel-group RCT. The subject recruitment will take place at nine selected outdoor smoking hotspots where many smokers will remain and smoke from July 2015 to January 2016. Informed consent will be obtained from all participants. The study flow and the schedule of the study procedures are indicated in Fig. 1 and Table 1, respectively. Our trial design has followed the SPIRIT checklist for standard protocol items (see Additional file 1).

**Fig. 1 Fig1:**
[figure not shown]
Flow of outreach interventions. *NRT* nicotine replacement therapy

**Table 1 Tab1:** Schedule of enrolment, interventions and assessments

	Study period					
	Enrolment	Allocation	Post-allocation			
Time point	Baseline	Baseline	1 week	1 month	3 months	6 months
Enrolment						
Eligibility screen	X					
Informed consent	X					
Allocation		X				
Interventions						
Intervention group		X				
Control group		X				
Assessments						
Socio-demographic	X	X				
Daily cigarette consumption		X	X	X	X	X
Intention to quit		X	X	X	X	X
Self-reported quitting outcomes			X	X	X	X
Perceived importance, confidence and difficulty to quit			X	X	X	X
Use of NRT			X	X	X	X
Biochemically validated quitting outcomes			X	X	X	X

*NRT* nicotine replacement therapy

### Subjects

Smokers with the following inclusion criteria will be invited to participate in our RCT: aged 18 years or older; smoked 10 cigarettes or more per day in the past week; able to read and speak Chinese; have not used NRT for the past 3 months; have no severe angina and serious cardiac arrhythmias; have not suffered an acute myocardial event in the past 4 weeks; and not pregnant and breastfeeding.

### Procedures

We will train the smoking cessation ambassadors for the subject recruitment and delivery of interventions to the subjects. Recruitment of outreach smoking cessation ambassadors will be conducted through sending mass mails to students of the University of Hong Kong. Retired nurses who are now providing counselling services in our existing smoking cessation projects will also be recruited. They will be invited to participate in a training programme about smoking cessation counselling and pharmacotherapy in assisting smokers to quit smoking. Our research team (comprised of physicians and nurses) will develop the training materials and intervention guides based on the principles of the US Agency for Health Care Policy and Research (AHCPR) guidelines [28] and the guidelines of the National Institutes of Health [29] and World Health Organization [30]. The training content will cover: the tobacco epidemic in Hong Kong; the health hazards of smoking; basic skills in assessing smoking dependence and quitting readiness; knowledge of smoking cessation medication (types of NRT, adherence, side effects, etc.); and brief counselling skills. At the end of the training, participants should be capable of delivering a brief smoking cessation intervention, which includes providing advice on using NRT.

Smoking cessation ambassadors will be paired up to approach the smokers and distribute souvenirs at the outdoor smoking hotspots in daytime. The souvenirs will include a small pack of tissue paper, with motivational messages (e.g. one in two smokers will be killed by smoking), quitline number (e.g. Quitline of Tobacco Control Office [name]) and other resources for smoking cessation services printed on the tissue-paper pack. If the smoker is willing to accept the souvenir and talk to the ambassador, one ambassador will ask further questions related to eligibility through an informal conversation. If the subject is eligible, the ambassador will introduce our RCT and NRT (about its side effects), seek his/her consent to participate and complete a one-page questionnaire on his/her behalf. The other ambassador will then randomize the subject by the sequentially numbered, opaque sealed envelopes (SNOSE) method.

### Interventions

The ambassador will help the subjects in the intervention group decide which type of NRT product (patch or gum) he/she can use and advise him/her on how to use the NRT based on his/her smoking habit and daily cigarette consumption. He/she will also be provided with an education card about NRT and a 12-page smoking cessation booklet (Fig. 1). Based on the experience of the previous trials [11, 31, 32], the choice of NRT (patch or gum) will be made according to the subject’s preference and the ambassador will provide medication counselling. Afterwards, the subjects will receive a free pack of 1-week NRT. If the subject is willing to continue the counselling at recruitment, the ambassador will introduce the NRT’s side effects, adherence and effectiveness (Table 2). Otherwise, the ambassador will contact the subject to provide such details and enquire about his/her usage of NRT by telephone within 2 days.

**Table 2 Tab2:** Counselling content for the intervention group

Part A: Introduction of NRT
1. Quitting smoking may cause withdrawal symptoms, such as irritability, insomnia, frustration, anxiety, restlessness and craving for cigarettes
2. Nicotine gum and patch can help relieve these symptoms
3. Nicotine products are far less dangerous than cigarette smoking
4. Scientific evidence strongly supports that NRT increases the quit rate and is a safe product.
Part B: Brief instruction for NRT patch
1. Apply patch on clean and dry skin on the chest, back, upper arms, hips, etc.
2. Apply one patch per day and remove before sleep
3. Change the patch site daily to avoid skin irritation
Part C: Brief instruction for NRT gum
1. Steps of chewing gum: slowly chew the gum 10–15 times → the taste gradually becomes stronger → park the gum in the buccal area for about 1–2 minutes → the taste gradually becomes lighter → repeat the above steps
2. Avoid soft drinks, coffee and fruit juice 15 minutes before chewing
3. Daily dosage should not be more than 15 pieces
Part D: Detailed instructions on NRT usage
1. Minor side effects may appear such as insomnia, skin irritation, jaw ache, hiccups and mouth soreness, but they will disappear after a few days
2. Make using NRT a daily habit
3. The standard medication period is 8 weeks. Suggest the participants continue medication after using all samples
4. Suggest the participants continue to use patch/gum even though feeling able to maintain abstinence
5. Must reduce or quit smoking during using patch/gum, otherwise it will increase the intake of nicotine
6. Tell others that you are using NRT, so that they can remind you to use it
7. Advise the participant to have healthy food intake and exercise to prevent weight gain during quitting
8. Our counsellor will call the participants to follow-up the usage after 1 week
9. Ask the participant to send back unused NRT to us in the enclosed envelope
10. Call the quitline ([name]) for further enquires

*NRT* nicotine replacement therapy

The control group subjects will be given the same advice on using NRT by the ambassador as the intervention group. The subjects will be suggested to purchase NRT on their own, but will not be given the sample. The same education card and the smoking cessation booklet will be provided.

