### Ethics, consent and permissions

The study protocol has been approved by the Institutional Review Board of the University of Hong Kong/Hospital Authority Hong Kong West Cluster (IRB reference number: UW 15-232). Written consent will be sought from all subjects to participate in this RCT, which will permit the investigators to disseminate the trial results and the study protocol via publications, without showing individual information.

All questionnaires will be stored in a cupboard with keys kept by the principal investigator and the research assistant only. The data will be kept for 10 years upon completion of the study. Electronic datasets of personal information and contact information will be encrypted and separated from the research dataset during the study period, and will be destroyed after the said storage period.

NRT has been proven an effective and safe aid for smoking cessation, which can be purchased over the counter in pharmacies or prescribed freely in smoking cessation clinics in Hong Kong. A common side effect of a nicotine patch is skin reaction. About 50 % of patients using the nicotine patch will experience a local skin reaction. The reaction is usually mild and self-limiting, but occasionally worsens over the course of therapy. Local treatment with hydrocortisone cream (1 %) or triamcinolone cream (0.5 %) and rotating patch sites may ameliorate such local reaction. In fewer than 5 % of patients, such reaction requires the discontinuation of the NRT. Other side effects are insomnia and/or vivid dreams. Common side effects of nicotine gum include mouth soreness, hiccups, dyspepsia and jaw ache. These effects are generally mild and transient, and can often be alleviated by correcting the patient’s chewing technique [13] or correcting the patient’s using habit. All subjects will be asked at telephone follow-up if they suffer from these side effects. If so, the counsellor will provide counselling on the usage. If the side effects are serious, the counsellor will ask them to cease usage.

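### Table 2's assurance that minor side effects, skin irritation included, will disappear is firmer than the protocol's own safety text, and no Table 2 item says what to do if a reaction persists or worsens (minor)

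*Protocol article*

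**What the plan says.** Table 2 of the protocol article (Interventions) lists the counselling content. Part D item 1 reads: "Minor side effects may appear such as insomnia, skin irritation, jaw ache, hiccups and mouth soreness, but they will disappear after a few days". The items around it are:

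- Part B item 3, a preventive step for the patch: "Change the patch site daily to avoid skin irritation".
- Part D items 2 to 4, on adherence: "Make using NRT a daily habit", "Suggest the participants continue medication after using all samples" and "Suggest the participants continue to use patch/gum even though feeling able to maintain abstinence".
- Part D items 8 and 10, which announce a counsellor's call after 1 week and give a quitline for enquiries.

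The section on ethics, consent and permissions describes the same skin effect. About 50% of patch users have a local reaction. Of its course the protocol says: "The reaction is usually mild and self-limiting, but occasionally worsens over the course of therapy". In fewer than 5% of patients, "such reaction requires the discontinuation of the NRT". All subjects are asked about side effects at telephone follow-up, and "If the side effects are serious, the counsellor will ask them to cease usage".

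**The concern.** Both places describe skin irritation from the patch, but with different certainty. The safety text speaks of what usually and what occasionally happens. The counselling line says that the effects will go away. A subject cannot tell at onset whether irritation will stay minor, so the line may be taken to cover a reaction that later worsens.

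Within Table 2 nothing says what to do in that case. The stop instruction that the article describes comes from the counsellor at a follow-up call. The scheduled call falls at 1 week, about when the 1-week sample runs out. An additional call within 2 days goes only to subjects who did not continue counselling at recruitment.

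What is at stake is accurate information for subjects and a possible delay in acting on a worsening local reaction. Controls are given the same advice on using NRT, so those who buy it may hear the same line. No outcome, power figure or analysis is affected.

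**Working it through.** **Text comparison**

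| Point | Table 2 (Interventions) | Ethics, consent and permissions |
|---|---|---|
| Course of the reaction | Minor effects will disappear in a few days | Usually self-limiting, occasionally worsens |
| Need to stop | Not mentioned | Fewer than 5% of patients |
| What to do | Rotate the site; 1-week call; quitline for enquiries | Counsellor asks at follow-up, advises on usage, and asks the subject to cease if serious |

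No item in Parts A to D mentions stopping, or calling because a reaction persists or worsens. The table does carry other usage limits: a maximum of 15 pieces of gum a day (Part C item 3) and reducing or quitting smoking while on NRT (Part D item 5). A stop-and-call line would therefore fit there.

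**Scale.** The plan gives no figure of its own to reproduce.

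Inputs from the article:
- 50 subjects in the intervention arm (Sample size determination)
- about 50% of patch users react; fewer than 5% must stop (Ethics, consent and permissions)
- 8-week standard medication period (Table 2, Part D item 3)
- 1-week sample (Interventions)

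Assumptions:
- 25 or all 50 of the arm choose the patch and use the whole sample
- risk is spread evenly over 8 weeks
- the 5% refers to all patch users and is taken at its ceiling

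Steps:
1. Share of reactors who must stop over a course: 0.05/0.50 = 0.10, so up to 1 in 10.
2. Whole-course ceiling: 25 × 0.05 = 1.25; 50 × 0.05 = 2.5.
3. One-week risk per user: 1 − 0.95^(1/8) = 0.0064.
4. Expected in the sample week: 25 × 0.0064 = 0.16; 50 × 0.0064 = 0.32.
5. Chance of at least one in the sample week: 1 − 0.95^(25/8) = 0.148; 1 − 0.95^(50/8) = 0.274.
6. The same with an assumed course rate of 2%: 1 − 0.98^(25/8) = 0.061; 1 − 0.98^(50/8) = 0.119.

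**Sensitivity**
- If the 5% refers to reacting patients only, step 1 falls below 1 in 20 and the expected counts halve, to about 0.08 to 0.16.
- If every such reaction fell in the first week, the count would be below 1.25 to 2.5. That fits poorly with a reaction said to worsen over the course of therapy.
- The share of reactions that worsen without requiring a stop is not given.

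**The case against.** The strongest reply is that the two texts need not conflict. The sentence in Table 2 opens with the word minor, so it can be read as covering mild effects only, and the ethics section also calls the reaction usually mild and self-limiting. This stands in part: the line is qualified, and the difference is one of firmness. It remains that skin irritation is named and that the promise of resolution carries no *usually*.

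A reader might infer that subjects are told to keep using NRT through a reaction. The documents do not support that. Part D item 2 is a general adherence message. Item 3 concerns continuing after the sample is used up, and item 4 concerns continuing despite feeling able to stay abstinent. That the assurance would discourage reporting is also only inference.

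A reader might also infer that subjects get no stop advice at all. That cannot be concluded. They receive an education card and a 12-page booklet, give written consent, and hear about side effects when the trial is introduced (Procedures). These texts are not shown, and stop advice could sit in any of them. The absence is established for Table 2 only.

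Safeguards also count. After each follow-up survey the interviewer discusses difficulties in using NRT (Outcomes). Adverse events are discussed at weekly meetings (Data quality control). Side effects are asked about at follow-up, with advice to stop if serious. These limit the harm, but they act once contact has been made. They do not correct the wording.

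**Conclusion.** The point holds as a minor one. Part D item 1 is firmer than the protocol's own account of the patch skin reaction, and Table 2 has no item for a reaction that persists or worsens. It does not amount to a flat contradiction, to an instruction to continue through a reaction, or to proof that stop advice is missing from the trial.

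The expected exposure is small: fewer than about 0.16 to 0.32 reactions that require stopping in the sample week, with a chance of at least one of at most about 15% to 27%. These figures rest on the assumed patch share, full use of the sample, even risk over 8 weeks and the 5% ceiling. The mismatch in wording depends on none of them.

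**What to change.** Keep the list of effects in Table 2 Part D item 1 and change the ending to: *usually settle within a few days; if a reaction persists or gets worse, stop using the product and call us without waiting for the next scheduled call*. Make the same change in the ambassadors' training, and check that the education card, booklet and consent text agree. On such a call the counsellor can advise the local treatment and site rotation already described in the ethics section, or a change to gum.

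The cost is one counselling line and the matching training sentence. The downside is that a few subjects may stop NRT for a reaction that would have settled; the call gives the counsellor a chance to limit this.
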